#### PREDICT sample size

For a prognostic model at least 20 EPV is needed to optimize reliability and to avoid bias in regression coefficients [37–39]. Based on having maximally 16 variables with a minimum of 20 events per variable, a prevalence of 30–40% after an initial sprain, including a 10% loss-to-follow-up, a sample size of 1185 patients is needed to perform the internal and 1185 patients is needed to perform the external model validation, resulting in a total of 2370 patients (Table 2).

During the study the required sample size may change and will be recalculated accordingly in case one of the following scenarios occur:In case one or more radiographic factors have a low inter- or intra-observer reliability (ICC ≤0.70), they will be excluded from the risk assessment model and the sample size will be recalculated using the new number of prognostic factors. If radiographic assessments cannot be performed in more than 2 cases (> 5%) a candidate predictor will be excluded, as the problem is likely to recur and therefore cannot be adequately assessed, now and during future assessment (e.g. up to 5% missing data is accepted) [40, 41].In case of multicollinearity between (ICC > 0.70) between prognostic variables one will be excluded;If a variable lacks agreement (ICC ≤0.70) with CAI it will be excluded;In case the prevalence of CAI during the study differs from the estimated 30%. In case the percentage of patients progressing to CAI exceeds the 50%, the sample size calculation will be based on the number of non-events. The prevalence will be recalculated when 500, 750, 1000, 1250, 1500, 1750,2000 and 2250 patients have returned the last questionnaire to minimize patient burden, as inclusion will stop as soon as the minimal required sample size is reached.

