**Fig. 6 Fig6:**
[figure not shown]
The Talar Convexity Angle (TCA) is formed by connecting the posterior talar tubercle (**a**), the most proximal part of the talus (**b**), and the deepest point of the transition to the talar neck (**c**)

Secondly, (12) age, (13) sex, (14) height, (15) BMI and (16) sports intensity (by means of the Ankle Activity Index (AAI)) will be implemented in the model as important patient characteristics, in case of a significant correlation. All these variables have shown a (prospective or retrospective) correlation with ankle instability in previous research apart from MDTA, MMHA and TCA. These three, however, have shown a relation with other pathologies that also concern an inversion-plantarflexion trauma mechanism and will therefore be explored on a potential correlation with CAI [14, 16, 30].

To assess overall recovery and CAI at 12 months, a questionnaire including patient reported outcome measures (PROMs) will be used. This questionnaire includes the FAOS and CAIT. The FAOS is a Dutch validated questionnaire assessing pain, other symptoms (swelling, locking, mobility, stiffness), function (activities of daily living) and sports and foot- and ankle related quality of life divided over 5 subscales, with scores ranging from 0 to 100 [31, 32]. The CAIT is scale consisting of 9-items measuring the severity of functional ankle instability per ankle individually. The total score ranges from 0 to 30 with a cut-off value discriminating between a functionally stable and instable ankle of 11.5 points (as calculated for the Dutch population) [33, 34].

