#### Prognostic value of variables

To determine whether the variables, selected from current literature, can be implemented in our model, it has to be determined whether they are of prognostic value on the progression of an ankle sprain to CAI. This will be done by determining whether they have an individual correlation with instability 12 months after an ankle sprain and whether this correlation is influenced using a multivariate analysis. In case of no existing correlation, factors are left out of the model and the sample size is recalculated accordingly.

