#### Inter- and intra-observer reliability

The inter- and intra-observer reliability will be analyzed using the Intraclass Correlation Coefficient (ICC) Two-Way Mixed model on absolute agreement in case of normally distributed data. Reliability is considered poor if the ICC is ≤0.40, moderate between 0.40 and 0.70, good between 0.70 and 0.90, and excellent > 0.90 [41]. In case of skewed data the Cronbach’s alpha will be calculated. In case of an ICC of > 0.70 a Bland and Altman plot will be drawn to visualize the measurements and their relation to the limits of agreement.

Additionally the Standard Error of Measurement (SEM: SD x √(1-ICC)) and Minimum Detectable Change (MDC_95%_: 1.96 x √2 x SEM) \ will be calculated to objectify the ICC.

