#### Prognostic value of variables

Depending on normality of data the Pearson or Spearman correlation coefficients will be used to assess correlations. A scatterplot for numerical data and Odds Ratio (OR) for binary data will be used to provide additional information on possible correlations in the data between prognostic factors. In case of correlations (*p* < 0.10 to avoid overfitting [40]) shown by an univariate analysis, a multivariate logistic regression will be performed to assess dependency between variables. The R^2^ will be used to visualize model fitness for the contribution of a factor to the progression to CAI and for the full model.

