### Missing data

A per protocol analysis is applied based on patients filling out at least one questionnaire and having an available AP and lateral radiograph for radiographic assessment. In case the last questionnaire is missing, on which the diagnosis of CAI will be based, and the question concerning persisting complaints at six or twelve months is not answered, differentiation between full recovery or progression to chronicity cannot be made. For this reason these patients and patients with a missing radiograph will be excluded.

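### The sample-size section excludes any predictor with an ICC of 0.70 or less with CAI; ICC is the wrong measure, almost no candidate could pass, and other sections select by a different rule

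*Protocol article*

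**What the plan says.** The sample-size section (PREDICT sample size) lists events that change the model and trigger a new sample-size calculation. The first concerns observer reliability and uses an ICC cut-off of 0.70. Two later items reuse the same coefficient and cut-off:

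- Predictor against outcome: "If a variable lacks agreement (ICC ≤0.70) with CAI it will be excluded".
- Predictor against predictor: "In case of multicollinearity between (ICC > 0.70) between prognostic variables one will be excluded".

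The only ICC the article defines is the one for observer reliability, under Data analysis and statistics: "Intraclass Correlation Coefficient (ICC) Two-Way Mixed model on absolute agreement in case of normally distributed data".

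Other sections select predictors differently:

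- Clinical outcome measures: patient characteristics "will be implemented in the model as important patient characteristics, in case of a significant correlation".
- Analyses, Prognostic value of variables: "In case of no existing correlation, factors are left out of the model", followed by a sample-size recalculation.
- Data analysis and statistics, Prognostic value of variables: "In case of correlations (*p* < 0.10 to avoid overfitting [40]) shown by an univariate analysis", the next step being a multivariable logistic regression.
- Data analysis and statistics, Prognostic model: variables significantly correlated with CAI go forward.

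The Discussion treats BMI and height as a special case and keeps whichever correlates more strongly with CAI.

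**The concern.** An ICC for absolute agreement asks whether two measurements of the same quantity give the same value. An ankle angle and a diagnosis are not two measurements of one quantity. The article itself reserves this ICC for normally distributed data, which a yes/no outcome is not. The 0.70 cut-off appears to have been carried over from the reliability criterion.

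Two things are at stake. First, the item decides which predictors survive, and a threshold that nothing realistic can reach does not select. Second, the list ties the number of surviving predictors to the sample size, and recruitment ends once that number is met. The retention rule therefore helps to set when inclusion stops. Two analysts following different sections could arrive at very different models and recruitment targets.

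**Working it through.** **1. The plan's own figures.** Inputs from the sample-size section: 16 candidates, 10 or 20 events per variable (EPV), 30–40% CAI, 10% loss. N = EPV × 16 / prevalence / 0.90.

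- 10 EPV: 160/0.30/0.90 = 592.6 (stated 593); at 40%, 444.4 (stated 445).
- 20 EPV: 320/0.30/0.90 = 1185.2 (stated 1185); at 40%, 888.9 (stated 889).
- Two data sets: 2 × 1185 = 2370, as stated.

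The arithmetic reproduces. With k surviving predictors the total at 30% is 2 × 20k/0.30/0.90 = 148.1k. That gives 2370 for k = 16, 1185 for k = 8 and 0 for k = 0.

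**2. Most lenient reading: ICC means plain correlation r.** For a normal predictor with a group difference of d SDs and CAI prevalence p, r = d√(p(1−p)) / √(1 + d²p(1−p)), and AUC = Φ(d/√2). Setting r = 0.70:

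- 30% CAI: d = 0.70/√(0.21 × 0.51) = 2.14, AUC = 0.93.
- 40% CAI: d = 0.70/√(0.24 × 0.51) = 2.00, AUC = 0.92.

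Conversely, an AUC of 0.65 means d = √2 × 0.385 = 0.545. At 30% CAI, r = 0.545 × 0.458/√(1 + 0.297 × 0.21) = 0.24.

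**3. ICC as the article defines it.** For two variables in a large sample, the absolute-agreement ICC is 2·cov / (s₁² + s₂² + (m₁ − m₂)²). The article gives no predictor means or SDs, so these are assumptions.

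- Age 35 (SD 14) against 0/1 CAI at 30%: even at r = 1 the ICC is 2 × 14 × 0.458/(196 + 0.21 + 34.7²) = 12.8/1400 = 0.009.
- MDTA 89 (SD 3): 2 × 3 × 0.458/(9 + 0.21 + 88.7²) = 2.75/7877 = 0.0003.
- Across assumed values for age, BMI, height, MDTA and talar radius, the ICC stayed at or below 0.01 even for a predictor with AUC 0.98. The consistency form of the ICC reached at most 0.38.

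**4. Binary predictor.** Sex, assumed 50/50. If every CAI case were of one sex, at 30% CAI the ICC is 2 × 0.15/(0.21 + 0.25 + 0.04) = 0.60, so sex cannot pass. At 40% the ceiling is 2 × 0.20/(0.24 + 0.25 + 0.01) = 0.80. With 90% of cases in one sex (odds ratio about 30) it is 2 × 0.16/0.50 = 0.64. A binary factor with 30% frequency at 30% CAI needs an odds ratio of about 40.

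**5. Distance from the competing rule.** With about 533 analysed patients (160/0.30), univariable p < 0.10 needs |r| of about 0.07; with about 1066 it needs about 0.05. The ICC item asks for 0.70, roughly ten times as much.

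**6. Collinearity item, same formula.** Distributions are again assumed.

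- Fibular position 8 (SD 3) mm, tibial width 35 (SD 3) mm. The percentage then has mean about 22.9 and SD about 8.8, and r is about 0.97. Covariance ≈ 9 × 100/35 = 25.7, so ICC ≈ 51.4/(9 + 77 + 221) = 0.17 (0.16 by simulation). A second set of assumed distributions gave 0.20 at r = 0.95, and 0.15 to 0.21 as r runs from 0.70 to 1.
- BMI 25 (SD 4) and height 175 (SD 10), taking r = 0.95: 76/(16 + 100 + 22500) = 0.003.
- Equal means and SDs, or standardised variables: the formula reduces to ICC = r, so such pairs are caught.

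**The case against.** The strongest reply is that the item sits in a list of recalculation triggers, not in the model-building section, and that four other places point to correlation with CAI. One of them, in Analyses, describes the same step in usable words. A sensible analyst would follow those, so a reader who infers that the plan yields no model goes too far. That stands: an empty model follows only if the ICC item is applied on top of the other rules. It is also fair that the two consequences are alternatives. If the rules stack, almost nothing survives; if they compete, the article does not say which wins. Neither outcome is acceptable, and no section withdraws the ICC item. A one-word slip is unlikely, since the sample-size section heads the prognostic-value step as an assessment of agreement. Reading ICC as correlation does not rescue 0.70 either (step 2).

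Three further points narrow the concern:

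- The p < 0.10 criterion is a screen for entry to the multivariable model, not a final retention rule.
- An ICC between two binary variables can be computed. It is unsuitable there, not undefined.
- On collinearity, a reader might infer that the rule misses every redundant pair. It does not: same-scale or standardised pairs are caught, and if ICC there means correlation the rule works. The article also examines correlations between prognostic factors, uses logistic regression to look at dependency, and handles BMI and height separately in the Discussion.

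**Conclusion.** The point holds in this form: the ICC-with-CAI exclusion is wrong as written and contradicts the selection rules elsewhere in the article. Under the most lenient reading, a candidate needs a single-predictor AUC of about 0.93 at 30% CAI (0.92 at 40%) to survive, assuming a normally distributed predictor. Under the ICC the article defines, the continuous predictors tried come nowhere near 0.70, and this does not depend on the exact means and SDs assumed. Applied literally, the item excludes essentially every candidate and makes the recalculated sample size degenerate. The other sections alone would yield a model, so the documents do not support saying that the plan as a whole produces none.

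The collinearity item is secondary. It fails for pairs on different scales under the absolute-agreement form, with an ICC of about 0.2 for the fibular pair at r of about 0.95. That figure is illustrative and rests on assumed distributions. The stated sample sizes of 593, 1185 and 2370 are not at fault.

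**What to change.** 1. Confine ICC to observer reliability.
2. Delete the ICC-with-CAI exclusion from the PREDICT sample size list. Refer instead to one pre-specified selection rule based on the logistic model, consistent with both Prognostic value of variables sections, and tie the recalculation to that rule.
3. Replace the ICC collinearity limit with a limit on the absolute Pearson or Spearman correlation, or on the variance inflation factor.
4. Reconcile that limit with the Discussion's rule for BMI and height, so that the choice between members of a flagged pair is stated once.

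The cost is a wording change, with no extra data or patients. It should be made before predictors are selected or the sample size is recalculated.

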### Data analysis and statistics

Demographics of the study population will be analyzed using the descriptive statistics. All statistics will be performed with SPSS version 23.0 (SPSS Inc., Chicago, IL, USA) and R package ‘Stats’ version 3.3.3 (University of Auckland, Auckland, New Zealand). A *p*-value of < 0.05 is considered significant. Normality of data will be assessed using the Shapiro-Wilks test.

#### Inter- and intra-observer reliability

The inter- and intra-observer reliability will be analyzed using the Intraclass Correlation Coefficient (ICC) Two-Way Mixed model on absolute agreement in case of normally distributed data. Reliability is considered poor if the ICC is ≤0.40, moderate between 0.40 and 0.70, good between 0.70 and 0.90, and excellent > 0.90 [41]. In case of skewed data the Cronbach’s alpha will be calculated. In case of an ICC of > 0.70 a Bland and Altman plot will be drawn to visualize the measurements and their relation to the limits of agreement.

Additionally the Standard Error of Measurement (SEM: SD x √(1-ICC)) and Minimum Detectable Change (MDC_95%_: 1.96 x √2 x SEM) \ will be calculated to objectify the ICC.

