### Analyses

#### Inter- and intra-observer reliability

Two radiology residents, an orthopedic resident and an emergency physician of the AMC will be included in the inter- and intra-observer reliability assessment. These professionals are selected because the orthopedic surgeon eventually treats the patient with CAI, and the emergency physician is the first to see a patient at the ER after a severe ankle sprain and the radiologists assess the radiographs. Radiologists are most experienced in radiographic assessment and are therefore be considered as reference standard, i.e. to assess inter-observer reliability the measurements by the orthopedic resident and emergency physician are compared to the measurements performed by the radiology residents. To assess intra-observer reliability 39 radiographs are assessed twice by each observer with a minimum of 2 weeks in between. In order to prepare the reliability assessment a calibration session will be held with all observers. If this proves the measurements can be performed reliably they will be implemented in the other participating hospitals after a calibration meeting and practice session.

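### Cronbach's alpha for skewed radiographic measurements is not a substitute for the absolute-agreement ICC, and measurements with inadequate agreement can pass the 0.70 limit if it is applied to alpha

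*Protocol article*

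**What the plan says.** Under Data analysis and statistics, the subsection on inter- and intra-observer reliability specifies an "Intraclass Correlation Coefficient (ICC) Two-Way Mixed model on absolute agreement in case of normally distributed data". It then switches statistic: "In case of skewed data the Cronbach’s alpha will be calculated". The trigger is given just above: "Normality of data will be assessed using the Shapiro-Wilks test", with p < 0.05 as the general significance level.

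The same subsection grades the ICC: "Reliability is considered poor if the ICC is ≤0.40, moderate between 0.40 and 0.70, good between 0.70 and 0.90, and excellent > 0.90". It also computes the standard error of measurement (SEM) as SD × √(1 − ICC) and the minimum detectable change (MDC) from the SEM.

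The section PREDICT sample size turns reliability into a selection rule. Radiographic factors with "low inter- or intra-observer reliability (ICC ≤0.70), they will be excluded from the risk assessment model", and the sample size is then recalculated. Limit, grades, SEM and MDC are all written in terms of the ICC. No limit for alpha is given.

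The earlier Analyses section describes the set-up: "Two radiology residents, an orthopedic resident and an emergency physician of the AMC will be included". The radiology residents act as reference, and "the measurements by the orthopedic resident and emergency physician are compared to the measurements performed by the radiology residents". For the intra-observer part, each observer reads 39 radiographs twice.

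**The concern.** A switch of statistic for skewed data should keep the quantity being estimated and change only how it is estimated. This one changes the quantity. Alpha uses the same variances and covariances as the ICC, so skewness gives no reason to prefer it. It leaves out systematic differences between observers, although offset from the radiology reference is a main thing the inter-observer comparison should detect. It also describes the mean of k readings, not one reading.

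The result decides which radiographic predictors stay in the model and whether the measurements go to the other hospitals. Two measurements with the same agreement could be treated differently because one failed a normality test. The model's cut-off values are also to be checked against the SEM and MDC, and both shrink if alpha is put in place of the ICC.

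**Working it through.** **Inputs from the protocol.** Exclusion at ICC ≤ 0.70; k = 2 readings for intra-observer reliability; four observers in total, so k = 2 to 4 for inter-observer reliability depending on how coefficients are formed; n = 39. The protocol gives no variance components or observer offsets, so those below are assumptions.

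**The plan's own figure.** With expected agreement 0.80 and relative error 0.20, 1/(0.20 × 0.80)² = 39.06, which matches the stated 39. The 0.70 limit is a convention with no derivation to reproduce.

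**What each statistic measures.** Let Vs be the variance between patients, Ve the residual error variance and Vb the variance between observers' mean levels.

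- Single-measure absolute ICC = Vs/(Vs + Vb + Ve)
- Average-measures absolute ICC = Vs/(Vs + (Vb + Ve)/k)
- Single-measure consistency ICC = Vs/(Vs + Ve)
- Alpha = Vs/(Vs + Ve/k)

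Vb does not appear in alpha, and Ve is divided by k.

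**Step 1: alpha of 0.70 on the single-reading scale.** Solving alpha = k·ICC/(1 + (k − 1)·ICC) gives ICC = alpha/(k − (k − 1)·alpha).

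- k = 2: 0.70/(2 − 0.70) = 0.54
- k = 3: 0.70/(3 − 1.40) = 0.44
- k = 4: 0.70/(4 − 2.10) = 0.37

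The k = 2 value is certain to apply to the intra-observer part. The others apply only if three or four observers are pooled in one coefficient.

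**Step 2: effect of a systematic offset.** Assume k = 2, Vs = 0.7 and Ve = 0.3, so each observer's readings have SD 1 and the consistency ICC is 0.70. An offset of d SD gives Vb = d²/2. Alpha is 0.7/(0.7 + 0.15) = 0.82 throughout.

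| Offset d | Vb | Single-measure absolute ICC | Average-measures absolute ICC | Alpha |
|---|---|---|---|---|
| 0.25 SD | 0.031 | 0.7/1.031 = 0.68 | 0.7/0.866 = 0.81 | 0.82 |
| 0.5 SD | 0.125 | 0.7/1.125 = 0.62 | 0.7/0.9125 = 0.77 | 0.82 |
| 1 SD | 0.5 | 0.7/1.5 = 0.47 | 0.7/1.1 = 0.64 | 0.82 |

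Against a single-measure ICC the decision differs in all three rows. Against an average-measures ICC it differs only at 1 SD.

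**Step 3: sampling at n = 39.** Simulation with gamma-skewed patient values, Vs = 1, Ve = 0.5 and k = 2 (offset in SDs of the true patient values; 4,000 runs) gave these chances of exceeding 0.70:

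| Offset | Single-measure absolute ICC | Average-measures absolute ICC | Alpha |
|---|---|---|---|
| 0 | 35% | 83% | 83% |
| 0.7 | 10% | 59% | 84% |
| 1 | 2% | 33% | 83% |

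**Step 4: SEM if alpha replaces the ICC.** In the step 2 example, alpha gives √(1 − 0.8235) = 0.42 SD. The single-measure absolute ICC gives √(1 − 0.622) = 0.61 SD at an offset of 0.5 SD and √(1 − 0.467) = 0.73 SD at 1 SD. The MDC is 1.96 × √2 times the SEM, so it shrinks in the same proportion.

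**The case against.** Four points count against a stronger statement, and each limits it.

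- **The limit is not written for alpha.** A reader might infer that the protocol lets unreliable measurements through. It does not say so: the 0.70 rule and the grades name only the ICC, and a limit for alpha may stand in a fuller document. Applying 0.70 to alpha is an inference, though the natural one. On the other reading the article gives skewed variables no exclusion rule at all. Even when 0.70 is applied, a poorly agreeing measurement can pass; it need not. The SEM and MDC point is conditional in the same way.
- **Single or average measures is not stated.** The 0.54 figure assumes single measures. If average measures are meant, both statistics rise with k, and without an offset they coincide (83% each in the simulation). Only the loss of absolute agreement remains.
- **Four observers do not mean k = 4.** A reader might conclude that a measurement in the protocol's poor band (0.37) would be kept. The text describes comparison with a radiology reference and does not commit to one pooled four-rater coefficient. At k = 2 the equivalent is 0.54, which is moderate on the protocol's scale.
- **Offsets are assumed and calibration is planned.** The protocol has a calibration session for all observers, then a calibration meeting and practice session at the other hospitals. These may make offsets small. The number of skewed variables is also unknown and could be zero.

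None of this makes alpha suitable. Planned calibration is itself a reason to use a statistic that can show whether it worked.

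**Conclusion.** The criticism of the method stands: alpha is the wrong fallback, because it answers a different question and skewness does not call for it. The consequence is conditional. If 0.70 is applied to alpha, measurements with inadequate agreement can be kept, and any SEM or MDC derived from alpha would be too small.

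The size depends on what the protocol leaves open. With a single-measure ICC and k = 2, the effective limit drops from 0.70 to 0.54 before any offset is counted. With an average-measures ICC the discrepancy comes only from offsets: it is negligible at 0.25 SD (0.81 against 0.82) and changes the decision at 1 SD (0.64 against 0.82) under the assumed variances. The documents do not support a claim that unreliable predictors will enter the model, or that poor ones would be kept by design. The point should be corrected before the reliability results are used to select predictors.

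**What to change.** Delete the sentence on Cronbach's alpha. State that the two-way mixed, absolute-agreement ICC, single-measure, is used for every continuous radiographic variable, for both inter- and intra-observer reliability. Where data are skewed, transform the measurement or report a bootstrap confidence interval for the same ICC. State that the 0.70 rule, the SEM and the MDC all refer to that ICC.

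This changes a sentence or two and needs no new data. The cost is that some measurements may be excluded that alpha would have kept, with the sample size recalculated as the protocol already provides. How to assess agreement on the three-level alignment class is a separate matter and does not affect this change.
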